**Fig. 1 Fig1:**
[figure not shown]
Modified CONSORT Flow Diagram

All teachers in each school selected for the cluster RCT and scale-up implementation study will be invited to complete the *iPLAY* intervention (or attention control intervention for 10 schools in the cluster RCT). However, only the student cohorts in Years 3 and 4 at baseline will complete outcome assessments (i.e., students in Years 3 and 4 at baseline, students in Years 4 and 5 at post-intervention [12 months], students in Years 5 and 6 at maintenance [24 months]). These students will be available for assessment at all time-points (c.f. most Year 5 and 6 students will leave the school by 24 months), and will have the cognitive ability to complete the questionnaires (c.f., Years 1 and 2). In addition, these years represent the ideal period to develop fundamental movement skill competency [30], which may help prevent the decline in physical activity typically observed during the transition from childhood to adolescence [31].

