#### Implementation timeline

Within each cohort, the main *iPLAY* intervention will be delivered in four phases that roughly equate to 3.5 school terms (see Fig. 2), which is approximately 10 months. In the RCT, the five *iPLAY* intervention schools from Cohort 1 will begin the intervention starting in August 2016 (Term 3), while Cohort 2 is scheduled for June 2017 (Term 2). In the scale-up implementation study, the 80 schools in Cohort 1 will be divided into 4 groups that will begin the intervention on a rolling basis – Group 1 (June 2016 – Term 2), Group 2 (August 2016 – Term 3), Group 3 (November 2016 – Term 4) and Group 4 (March 2017 – Term 1). A similar roll-out is scheduled for Cohort 2, starting in June 2017. See Fig. 3 for details.

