##### Academic achievement

We will work with NSW BOSTES to obtain students’ Year 3 and 5 NAPLAN numeracy and literacy standardized test scores [60].

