### Scale-up implementation evaluation

Running alongside the cluster RCT will be a scale-up implementation study. This evaluation will be a multiple cohort design, with all schools receiving the intervention. Measurement will be guided by the RE-AIM framework [73] and will occur at baseline, 12 and 24 months for each cohort.

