#### Participants and procedures

Participants will include principals, teachers and students at government-funded primary schools in NSW. There will be no exclusion criteria for principals or teachers within these schools. To be included in the study at least 50 % of Stage 2 (Years 3 and 4) teachers must be willing to participate in the program, at least one staff member must be willing to be an *iPLAY* leader, and the principal must provide consent for the program to run in the school. All students who are enrolled in Years 3 or 4 (Stage 2) at baseline and who are able to participate in physical activity will be eligible for the study, except for students enrolled in ‘Schools for Specific Purposes’ (i.e., for students who require intensive levels of support). In these schools, teachers will be eligible to participate in the study, but students will not be asked to complete outcome assessments.

Principals and teachers will provide written informed consent to participate in the scale-up implementation study. Passive consent procedures will be used regarding student participation; newsletters will be sent home and will ask parents to indicate if they do not wish their child to participate in the study.

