#### Statistical analyses

The scale-up implementation study will be assessed with a focus on descriptive statistics concerning reach, adoption, implementation, and maintenance. We will also use linear regression to explore the impact of school and community characteristics on program reach. We will use linear mixed model analysis to examine changes in outcome variables from baseline to 12-months and 24-months (i.e., effectiveness). These effects will be estimated for the entire sample as well as in key sub-populations (e.g., across teacher sex, school average SES, teachers with high vs low internet self-efficacy). Where possible, we will compare *iPLAY* schools with expected values within the population (e.g., NAPLAN scores in similar schools, physical activity participation) from other data sources such as NSW School Physical Activity and Nutrition Survey [66]. We will also compare outcomes at 12 months (post-intervention) for Cohort 1 with baseline levels for Cohort 2, taking advantage of the natural experiment that is inherent in the design of the study.

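### The scale-up study's cohort comparison sets treated pupils against untreated pupils about one school year younger, so for pupil outcomes it cannot separate ageing from an iPLAY effect

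*Protocol article*

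**What the plan says.** The contrast is in the Protocol article, at the end of Statistical analyses under Scale-up implementation evaluation: "We will also compare outcomes at 12 months (post-intervention) for Cohort 1 with baseline levels for Cohort 2". The sentence goes on to justify it as "taking advantage of the natural experiment that is inherent in the design of the study".

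Four other places fix who is on each side:

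- The Design section (text after Fig. 1) sets the assessed year groups: "students in Years 3 and 4 at baseline, students in Years 4 and 5 at post-intervention [12 months". The paragraph covers both studies, since it opens with "All teachers in each school selected for the cluster RCT and scale-up implementation study will be invited".
- Participants and procedures, for the scale-up study, repeats the eligibility rule: "All students who are enrolled in Years 3 or 4 (Stage 2) at baseline".
- The opening of Scale-up implementation evaluation says that measurement "will occur at baseline, 12 and 24 months for each cohort".
- Implementation timeline places the second cohort about a year after the first: "A similar roll-out is scheduled for Cohort 2, starting in June 2017", against June 2016 for the first group of Cohort 1.

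No section limits the comparison to a common school year, and none mentions adjustment for age or year level.

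**The concern.** Starting Cohort 2 about a year later puts Cohort 1's 12-month assessment and Cohort 2's baseline at roughly the same calendar time. That is the attraction of the comparison. But the same children are followed, so by 12 months Cohort 1 pupils have moved up a grade, while Cohort 2 pupils enter at the original grades. Calendar time is aligned; age and schooling are not.

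The scale-up study has no control arm. Its within-cohort change from baseline to 12 months already contains a year of ageing, and a reader would expect the cohort comparison to remove that. For pupils it does not. This is also the only planned contrast with untreated schools recruited by the same study; the other comparators in that section are external, such as population survey values and similar schools. A pupil difference reported from it as an effect of iPLAY could be partly or wholly a grade difference, or a real effect could be hidden by one.

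**Working it through.** The plan gives no sample size, power or effect figure for this contrast, so there is nothing to reproduce. The check is arithmetic on school years.

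**Inputs.** Cohort 1 at 12 months: Years 4 and 5. Cohort 2 at baseline: Years 3 and 4 (Design; Participants and procedures). Let p1 and p2 be the shares of pupils who were in Year 3 at baseline in Cohorts 1 and 2. The document gives neither.

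**Mean school year.**
- Cohort 1 at 12 months: 4·p1 + 5·(1 − p1) = 5 − p1
- Cohort 2 at baseline: 3·p2 + 4·(1 − p2) = 4 − p2
- Gap: (5 − p1) − (4 − p2) = 1 + p2 − p1

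**Results.**
- Same split in both cohorts (p1 = p2): gap 1.0. With an even split, 4.5 − 3.5 = 1.0.
- p1 = 0.6, p2 = 0.4: gap 0.8.
- p1 = 0.4, p2 = 0.6: gap 1.2.

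**Overlap.** Only Year 4 is on both sides. Cohort 1 pupils in Year 5 (share 1 − p1) and Cohort 2 pupils in Year 3 (share p2) have no same-grade counterpart. That is half of each side with an even split, or 40% to 60% over the assumed range.

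**Restricted to Year 4.** The gap is 4 − 4 = 0.

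**Could a small ageing trend matter? (illustration only)** The document gives no yearly change for any scale-up outcome, so the slopes are assumptions. So are 80 analysed schools per cohort, 1.5 to 3 classes of 18 pupils per school (27 to 54 pupils), and a school intraclass correlation of .01 to .05. The class value of .09 is borrowed from the trial's fitness outcome, which the scale-up study does not measure. With S schools per side, c classes per school and m pupils per class:

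SE² = 2·[ICC(school)/S + ICC(class)/(S·c) + (1 − ICC(class) − ICC(school))/(S·c·m)]

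As a check on the formula, the trial's own design (S = 10, c = 3, m = 18, effect .35, two-sided 5% assumed) gives power 0.908, against the stated .91.

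- Smallest SE (c = 3, school ICC .01): √[2·(0.01/80 + 0.09/240 + 0.90/4320)] = 0.0376
- Largest SE (c = 1.5, school ICC .05): √[2·(0.05/80 + 0.09/120 + 0.86/2160)] = 0.0596

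With no true effect and a grade difference of b SD, the chance of a significant result is Φ(b/SE − 1.96) + Φ(−b/SE − 1.96):

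- b = 0.05: 13% to 26%
- b = 0.10: 39% to 76%
- b = 0.20: 92% to 100%

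The nominal rate is 5%. With this many schools, even a modest grade trend could pass for an effect. These rates do not show that such a trend exists.

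**The case against.** The strongest reply is that this is one supplementary sentence in a study whose analysis is mainly descriptive and whose effectiveness component is expressly reduced. Effectiveness is the task of the cluster trial, where both arms age together. The article is also condensed: it names the contrast but not the model, and an unseen analysis plan may adjust for age. Date of birth is among the student questionnaire items, and the scale-up study uses all the trial's questionnaires, so adjustment is feasible.

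The point about importance stands and sets the severity. The point about missing detail stands only in part. The article names both sides of the comparison and interprets it as a natural experiment; followed as written, it is confounded for pupils. Adjustment would help, but Year 5 exists only among treated pupils and Year 3 only among untreated ones, so anything beyond the Year 4 comparison rests on an assumed age trend.

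Stronger readings that a reader might draw are not supported:

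- *The whole comparison fails.* Teacher and principal questionnaires are also scale-up outcomes, and pupil grade does not shift them in this way.
- *The bias favours iPLAY, or is known to mask it.* No ageing slope is given. The decline in activity that the Design section cites belongs to the move from childhood to adolescence, not to Years 3 to 5.
- *NAPLAN will be compared across two grades.* The Academic achievement section obtains "Year 3 and 5 NAPLAN numeracy and literacy standardized test scores" but does not assign them to time-points. The contrast does not name NAPLAN, and the preceding sentence gives it another comparator, similar schools. What can be said is that the shared grade, Year 4, has no score.

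**Conclusion.** The concern holds for pupil outcomes in the scale-up study. The two sides differ by about one school year: 1.0 if the cohorts share a year split, 0.8 to 1.2 if the Year 3 share varies separately between 40% and 60%, which is an assumption. As written, the contrast cannot separate ageing and schooling from an iPLAY effect. The bias on any outcome scale, and its sign, cannot be derived from the document. Because the contrast is supplementary and leaves the randomised trial and the teacher and principal outcomes untouched, this should be fixed but is not critical.

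**What to change.** Change the wording of this one analysis:

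- For pupil outcomes, compare Cohort 1 pupils in Year 4 at 12 months (Year 3 at baseline) with Cohort 2 pupils in Year 4 at baseline, using a model with a school random effect.
- Keep an all-pupil model adjusted for school year or age as a sensitivity analysis, noting that it relies on the assumed trend outside Year 4.
- State that NAPLAN is not part of this contrast, and keep the comparison with similar schools already planned for it.
- Leave teacher and principal outcomes as planned.

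**Cost.** No new data are needed. About half of the pupils leave this contrast. Under the illustrative assumptions above, going from 3 to 1.5 classes per school raises the standard error from 0.0376 to 0.0508 (school ICC .01; ratio 1.35) or from 0.0490 to 0.0596 (school ICC .05; ratio 1.22). The comparison remains non-randomised between schools recruited at different times, and should be reported as such.

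The trial's control schools are not needed as an extra benchmark. They are offered My Science, are chosen as closely matched pairs, and use written parental consent and trained assessors, whereas the scale-up study uses passive consent and teacher-administered questionnaires.

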#### Economic evaluation

The research question for economic evaluation of the scale-up implementation study will be to assess, from a societal perspective, the cost-outcome of scaling up the *iPLAY* project (rollout and implementation to 160 schools) in primary schools within NSW to assess intervention affordability and sustainability.

The economic analysis will be a cost-outcome description as the one-arm design of the scale-up implementation study does not include a control arm (which is necessary for determination of comparative cost-effectiveness). The primary economic analysis will comprise three components: a cost analysis; an outcome analysis and the relationship between cost and outcomes for the intervention. Costing of the intervention using opportunity cost principles will involve the following steps:Identification of costs to be included, using ‘pathway analysis’, where activities in all stages of the roll out of the *iPLAY* project are fully specified; A societal perspective and steady state operation of the intervention will be assumed (up and running to its full effectiveness potential). Costs will largely relate to the time costs of specialist mentors, leaders, classroom teachers, and school principals (using opportunity cost principles). Any administrative resources used at the program management level also will be identified and included, although research-driven activities will be separated from the activities that would be carried out should the program be adopted by primary schools;Measurement of the resources consumed in natural units (number of hours spent by specialist mentors/leaders within school/principals to deliver the intervention, number and length of school visits, etc.);Valuation of these resources in monetary units (using 2018 as the reference year).

In addition, variations in delivery costs of the *iPLAY* intervention between participating schools will be identified in order to determine any factors that may impact on the roll out of this program throughout NSW primary schools and its adoption in other jurisdictions.

The economic outcomes for the scale-up implementation study will be presented as total costs, average costs per child and per school, separately from the intervention and maintenance periods. The relationship between costs and outcomes will be reported as average cost per outcome.

## Discussion

The purpose of this study is to evaluate the extent to which an existing, efficacious physical activity intervention can be scaled-up and disseminated widely using online learning methods alongside face-to-face implementation support. A web-based delivery system is attractive as it may support scaling-up and sustainability. However, little, if any, evidence exists regarding the effectiveness of comprehensive primary school-based physical activity interventions delivered using online methods. Using two concurrent studies, and guided by the RE-AIM framework, our project will help provide evidence on the effectiveness and cost-effectiveness of teacher professional learning delivered largely via the Internet to address the issue of physical inactivity among primary school-aged children.

## Abbreviations

BMI, body mass index; BOSTES, Board of Studies, Teaching and Educational Standards; iPLAY, Internet-based Professional Learning to help teacher support Activity in Youth; MVPA, moderate-to-vigorous physical activity; NAPLAN, National Assessment Program – Numeracy and Literacy; PE, Physical Education; RCT, randomized controlled trial; RE-AIM, Reach Effectiveness – Adoption Implementation Maintenance; SCORES, Supporting Children’s Outcomes using Rewards, Exercise and Skills; SES, socioeconomic status; WHO, World Health Organization
